#### Safety assessment and adverse events reporting

2.4.4

We will evaluate liver function, albumin, renal function, calcium, phosphorus, potassium, sodium, chloride, and other biochemical parameters at baseline and post-intervention to evaluate the safety of the HDVD. All adverse events reported during the study will be closely monitored and recorded. In this trial, an adverse event is any unfavorable or unexpected occurrence related to the intervention. The investigator will ask the participants questions regarding adverse reactions. Participants will be called on days 1, 3, and 7 after each injection to determine any adverse events (**Table 3**). Moreover, participants will be asked to self-report any adverse events at any time. All adverse events will be professionally addressed, closely monitored by a physician, and treated as necessary. Serious adverse events will be reported to the study director—responsible for managing adverse reaction reports—within 1 h. Additionally, related serious adverse events will be reported to the Ethics Committee of Longyan First Affiliated Hospital of Fujian Medical University. The Ethics Committee is independent of the investigators, and the investigators are not members of the Ethics Committee.

**Table 3 T3:** Safety assessment and adverse event follow-up of participant.

	M0	M1	M2	M3
Liver function: alanine aminotransferase, aspartate aminotransferase, total bilirubin, albumin, globulin	√			√
Renal function: creatinine, blood urea nitrogen, and eGFR calculated by the CKD-EPI equation	√			√
Creatine kinase (CK), creatine kinase myocardial band (CK-MB), lactate dehydrogenase (LDH), alkaline phosphatase (ALP)	√			√
Electrolytes: calcium (Ca), phosphorus(P), potassium(K), magnesium (Mg), sodium (Na), chloride (Cl)	√			√
Closely follow up on the physical health after injection, and receive consultation and feedback at any time within 24 h	√	√	√	√
Did the participant experience any adverse reactions after the injection (whether or not determined to be related to this injection)	√	√	√	√
Digestive adverse reactions: decreased appetite, constipation or diarrhea, abdominal pain, nausea, or vomiting	√	√	√	√
Skin adverse reactions: pruritus, allergic dermatitis, rash, swelling, and pain at the injection site	√	√	√	√
Nervous system adverse reactions: metallic sensation in the mouth, persistent headache, convulsions, and insomnia	√	√	√	√
Urinary adverse reactions: cloudy urine, nocturnal polyuria, and hematuria	√	√	√	√
Skeletal system adverse reactions: bone pain and myalgia	√	√	√	√
Respiratory and circulatory system: shortness of breath, palpitations, hypertension, shock, hypotension, and chest pain	√	√	√	√
Hematologic and endocrine adverse reactions: rapid weight loss or gain, fever, and fear of cold	√	√	√	√
Other adverse reactions: fatigue, asthenia, dry mouth, and fall	√	√	√	√
Record treatment for adverse reactions (only for participants with adverse events)	√	√	√	√

M0, baseline assessment; M1, 1 month from baseline; M2, 2 months from baseline; M3, 3 months from baseline; eGFR, estimated glomerular filtration rate; CKD-EPI, the Chronic Kidney Disease Epidemiology Collaboration equation.

### Data management

2.5

After enrollment, all participants will be given a unique identification number, which will substitute participants’ names in the database to protect their privacy. All data will be entered using the EpiData Software (Version 3.1, Denmark), and two data entry clerks will enter the case report form into the same database and cross-check to ensure the accuracy of the data. Finally, all written materials and encrypted electronic files containing the study’s data will be stored and backed by the study director. These documents will be retained for > 3 years after this study.

### Data analysis

2.6

Any participant who completes the randomization will be included in the intention-to-treat set for data analysis. In cases when random or unforeseeable missing data occur, the missing data will be processed by multiple imputation method and sensitivity analysis will be carried out (49). The safety set which contains at least one safety assessment and adverse event report will be used to analyze the safety of HDVD supplementation. Quantile-quantile plot will be used to determine if the data conforms to a normal distribution. For descriptive analysis, the results of continuous variables (age and body mass index, among others) that conform to normal distribution will be expressed as mean ± standard deviation, and those that do not conform to normal distribution will be expressed as median and interquartile range. Categorical variables (sex and smoking status) will be expressed as frequencies and percentages.

Baseline data will be compared between the HDVD supplementation and placebo control groups. In HDVD supplementation or placebo control group, a paired sample t-test will be used for post-intervention versus pre-intervention comparisons. The difference value of MNSI before and after intervention will be performed by independent sample t-test test to compare the difference between the two groups. If the data does not conform to normal distribution, the Mann-Whitney U test will be used for analysis. The chi-square test will be used for categorical variables.

Furthermore, we will use the MNSI score before intervention as a covariate, and the F value will be calculated using analysis of covariance (ANCOVA) to analyze the change in the MNSI score after HDVD supplementation. Finally, if the number of adverse events occurring during the study is sufficient, the chi-square test or Fisher’s exact probability method will be used to compare differences in adverse events between both groups.

All data will be analyzed using the R software (version 4.1.2; R Foundation for Statistical Computing, Vienna, Austria). Additionally, all statistical analyses will be performed using a two-sided test, considering P < 0.05 statistically significant.

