## Abstract

**Background:**

Distal symmetric polyneuropathy (DSPN) is the most common chronic complication of type 2 diabetes mellitus (T2DM). DSPN may lead to more serious complications, such as diabetic foot ulcer, amputation, and reduced life expectancy. Observational studies have suggested that vitamin D deficiency may be associated with the development of DSPN in T2DM. However, interventional studies have found that low-dose vitamin D supplementation does not significantly improve neuropathy in DSPN. This study aims to evaluate the efficacy and safety of intramuscular injection of high-dose vitamin D (HDVD) in T2DM with DSPN combined with vitamin D insufficiency.

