Many researchers have explored whether increasing the dose of vitamin D supplementation will cause side effects or adverse reactions. In a study by Binkley et al. (37) administering 50000 units of vitamin D monthly to people aged > 65 years did not cause any toxicity or side effects. Another clinical study by Bian et al. (61) in people aged > 80 years showed that supplementation with 600000 units of vitamin D monthly for more than half a year might be safe. However, the sample size used in these studies was small. Therefore, we will use a monthly regimen of high-dose intramuscular vitamin D injections closely observed by the implementer to achieve better compliance and an earlier time to target. Additionally, our study will address the safety of monthly HDVD supplementation in individuals with insufficient vitamin D levels.

Although vitamins D_2_ and D_3_ have the same efficacy in exerting physiological effects, previous studies have suggested that vitamin D_2_ supplementation may affect vitamin D_3_ levels (56). This may be related to increased CYP24A1 enzyme activity in the liver, promoting the conversion of 25(OH)D_3_ to 24,25-(OH)_2_D_3_, thereby inactivating it (57, 62). Additionally, 25(OH)D_2_ and 25 (OH)D_3_ compete for the binding to VDBP (63, 64). Notably, traditional immunoassays for vitamin D do not distinguish between 25(OH)D_2_ and 25(OH)D_3_, which may underestimate 25(OH)D_2_ levels. Testing for vitamin D_2_ can rule out the effects of sunlight (65). Therefore, we will use the gold standard LC-MS/MS method to distinguish between 25(OH)D_2_ and 25 (OH)D_3_ levels.

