The strength of this study design is that it will determine whether an improvement in neuropathy accompanies an increase in vitamin D concentration due to HDVD supplementation. Notably, DSPN is associated with muscle atrophy; thus, decreasing the quality of life. Although previous studies suggested that vitamin D supplementation may improve muscle strength (52, 54, 66), our study will explore the effects of HDVD from multiple dimensions, such as quality of life and muscle strength. We will use the Short Form-12 (SF-12) questionnaire, comprising eight domains, to assess the quality of life. The SF-12 has satisfactory validity and reliability, showing good internal consistency in the psychological (Cronbach’s α=0.83) and physical component summaries (Cronbach’s α=0.81) (67). Moreover, we will measure the maximum grip strength of both hands before and 3 months post-intervention to assess changes in muscle strength.

This study design has some limitations. First, the trial will be conducted only in China’s population with T2DM and DSPN. Therefore, the results may not be directly applicable to other ethnic groups. Second, the latitudes of southern China will be selected for this study; therefore, the results may not be directly applicable to other latitudes. Nevertheless, the study can provide certain evidence that may require further verification in other regional or international multicenter studies. Third, owing to the difficulty in recruiting patients with DSPN, it will be difficult to maintain a balance between the groups. However, we will further correct factors, such as age, sex, and body mass index, through stratified analysis and by applying the analysis of covariance statistical strategy as far as possible.

In conclusion, this study will provide clinical evidence demonstrating the efficacy and safety of post-treatment HDVD supplementation for DSPN. Additionally, if HDVD supplementation can improve neuropathy, this study will provide new directions for future pharmacological research and clinical management of diabetic neuropathy.

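### The only planned between-arm comparison of adverse events depends on an undefined condition and yields a test without an effect estimate or interval

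*Protocol article*

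**What the plan says.** Safety appears among the aims in several places of the protocol article. The Abstract (Background) states: "This study aims to evaluate the efficacy and safety of intramuscular injection of high-dose vitamin D". The Discussion adds that "our study will address the safety of monthly HDVD supplementation in individuals with insufficient vitamin D levels".

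Section 2.6 (Data analysis) defines the analysis population without any condition: "The safety set which contains at least one safety assessment and adverse event report will be used to analyze the safety of HDVD supplementation". It also has a general descriptive rule: "Categorical variables (sex and smoking status) will be expressed as frequencies and percentages".

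The rule for comparing the arms on adverse events closes the methods in that section. It applies only "if the number of adverse events occurring during the study is sufficient". In that case the chi-square test or Fisher's "exact probability method will be used to compare differences in adverse events between both groups". The article does not say how many events would be enough, who decides, or what happens otherwise. It names no risk difference, risk ratio or confidence interval for adverse events in either case.

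Section 2.4.4 and Table 3 schedule laboratory safety tests at baseline and month 3, and adverse event follow-up at every visit. Neither depends on an event count.

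**The concern.** The condition is a rule that the article states, so it is not a detail left to a fuller document. It has two weaknesses.

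- Whether the arms are compared is decided from the trial's own data, against a standard that is never defined. Two analysts with the same data could decide differently.
- The planned result is a P value only. When events are few, a P value says little, and a skipped test says nothing. The useful quantity is then an interval for the difference, because it shows what excess the data cannot exclude.

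The stated safety aim could therefore end with two columns of counts and no planned statement of the between-arm difference or its uncertainty. The condition also has no technical basis, because Fisher's exact test, named in the same sentence, is valid at any count.

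**Working it through.** **Inputs.** From section 2.1.3: effect 1.19 points, SD 1.29, two-sided alpha 0.01, power 0.95, 42 per group before dropout, 20% dropout, 53 per group enrolled. From section 2.6: two-sided P < 0.05 for all tests. The event splits below are illustrative assumptions, since the article gives no expected adverse event rate.

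**Arm size, reproduced first.** Normal approximation, 1:1 allocation:

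n = 2 × [1.29 × (2.576 + 1.645) / 1.19]² = 41.87, rounded up to 42 per group (84 in total).

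42 / (1 - 0.20) = 52.5, rounded up to 53 per group (106 in total).

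Both agree with the article, so a safety comparison will have roughly 42 to 53 patients per arm.

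**No events in an arm.** The exact two-sided 95% upper limit for 0 of n is 1 - 0.025^(1/n):

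- n = 53: 6.7%
- n = 42: 8.4%

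**Fisher's exact test, k v 0 events, n per arm.** With equal arms the two-sided P is 2 × C(n,k) / C(2n,k) for k ≥ 1. For k = 4 and n = 53 this is 2 × C(53,4) / C(106,4) = 0.118.

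| Split | P, 53 per arm | P, 42 per arm |
|---|---|---|
| 3 v 0 | 0.243 | 0.241 |
| 4 v 0 | 0.118 | 0.116 |
| 5 v 0 | 0.057 | 0.055 |
| 6 v 0 | 0.027 | 0.026 |

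With no events in the other arm, the test first falls below 0.05 at 6 v 0.

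**Risk difference with Newcombe 95% CI, 53 per arm.** The method combines the Wilson limits (l, u) of each arm:

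lower = d - √[(p1 - l1)² + (u2 - p2)²]; upper = d + √[(u1 - p1)² + (p2 - l2)²]

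For 4 v 0: p1 = 4/53 = 0.0755 with Wilson limits 0.0297 to 0.1786; p2 = 0 with limits 0 to 0.0676. Then d = 0.0755.

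- Lower: 0.0755 - √(0.0457² + 0.0676²) = 0.0755 - 0.0816 = -0.006
- Upper: 0.0755 + √(0.1031² + 0²) = 0.179

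That is 7.5 points (95% CI -0.6 to 17.9). Other splits by the same formula:

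| Split of 53 v 53 | Difference, points | 95% CI, points |
|---|---|---|
| 0 v 0 | 0.0 | -6.8 to 6.8 |
| 1 v 0 | 1.9 | -5.0 to 9.9 |
| 3 v 0 | 5.7 | -2.1 to 15.4 |
| 3 v 1 | 3.8 | -5.1 to 13.6 |
| 5 v 0 | 9.4 | 0.8 to 20.3 |

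An estimate and an interval therefore exist at every count, including no events at all. Few events are no reason to omit the comparison.

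**The case against.** The strongest reply is that the condition controls a hypothesis test and not the reporting of safety. The safety set is unconditional, categorical variables are to be shown as frequencies and percentages, and laboratory values are collected in everyone. From per-arm counts a reader can subtract. Describing sparse events without testing them is a defensible choice, and the layout of safety tables and the choice of interval are often left to an analysis plan that is not shown here.

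Much of this stands. The point concerns the adverse event comparison only, and leaving out a P value for sparse events would be no fault. What remains is that the article fixes a rule, and the rule is poor: it is undefined, it depends on the data, and it is the only between-arm method tied to adverse events. Subtracting two counts gives a difference but no interval. The general sentence on chi-square tests for categorical variables does not help, because the adverse event sentence is the specific rule.

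Three stronger readings are tempting, and the article does not support them.

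- **That few events will be reported as proof of safety.** Section 2.6 says no such thing. The closing line of the Discussion, "this study will provide clinical evidence demonstrating the efficacy and safety of post-treatment HDVD supplementation for DSPN", is an expectation and not an analysis rule.
- **That safety ranks equally with efficacy.** The two are named together as aims, but section 2.4.1 makes the change in MNSI score the only primary outcome, and the sample size rests on an MNSI score.
- **That the condition invites selective reporting.** Its wording reads as the total number of events. Fisher's test conditions on that total, so a decision based on the total alone does not bias it. A problem would arise only if sufficiency were judged with the split between arms in view, which the text neither says nor rules out.

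**Conclusion.** The point holds in a limited form and is minor. The only between-arm adverse event comparison in section 2.6 rests on an undefined, data-dependent condition, and it would deliver a test without an estimate or interval even when the condition is met. Per-arm counts and laboratory values may still appear.

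The size of what could go unreported is shown by the 4 v 0 example: a non-significant test alongside an excess of up to about 18 points that is not excluded. This rests on 53 analysed per arm and an assumed split. With 42 per arm the same kind of interval is wider: for 3 v 0 it runs from -2.5 to 19.0 points, against -2.1 to 15.4 with 53. Neither the sample size nor the primary analysis is affected.

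**What to change.** In section 2.6, delete the condition on the number of events. State that, in the safety set, the following will always be reported by arm: the number and percentage of participants with at least one adverse event, and the same for at least one serious adverse event. Each should carry the risk difference and a 95% CI suited to small counts, with the method (Newcombe or exact) named in advance. Fisher's exact test can be kept as supportive.

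The cost is one revised sentence and a few table columns. The intervals will be wide at this sample size, which is itself information the reader needs. Near the boundary the interval and the test can disagree: at 5 v 0 of 53, the Newcombe interval excludes zero (0.8 to 20.3 points) while Fisher's P is 0.057. The text should therefore say that the interval is the main result and the P value is supportive.

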### Data monitoring

2.7

This study will be supervised by the Ethics Committee of the Longyan First Affiliated Hospital of Fujian Medical University, whose members have no conflicts of interest with this study. The study director will have access to all results and decide when to terminate the study based on its progress. Additionally, the study director will grant other members of the study’s team the right to disseminate the trial results by publishing papers.

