### Randomization, allocation concealment and blinding

2.2

All eligible participants will be assigned a unique identification number in the order of enrollment. Randomized assignment of subjects is fundamental to clinical trial design. While performing a simple sequence of random numbers can ensure independence among subjects and avoid potential selection biases, doing so has the potential to lead to an imbalance in the distribution of important covariates across treatment groups. Therefore, we will opt for the block randomization scheme (47). A person independent of the research center will generate a block randomization coding scheme using R software (version 4.1.2, R Foundation for Statistical Computing, Vienna, Austria). Next, all participants will be assigned in a 1:1 ratio to the placebo control or HDVD supplementation groups.

In order to avoid selection bias to the maximum extent possible, we will adopt the method of avoiding leakage of grouping information. The goal is to balance out all known and unknown factors between the two groups, so that differences in outcomes between the groups could ultimately be attributed to the effect of HDVD supplementation. To this end, we are going to use the method of allocation concealment. A staff member who determines the grouping of random sequences will not be involved in the inclusion of subjects. Neither our investigators nor our subjects are aware of the random sequence and the corresponding group during the diagnosis of DSPN, during the eligibility evaluation stage such as reviewing whether patients met the inclusion and exclusion criteria, and during the stage of soliciting patients’ willingness to participate in the trial.

Each protocol will be placed in an opaque envelope, marked with the code, and sealed. In order to reduce information bias, including measurement bias and implementation bias, we will double-blind the trial for the investigator and participants. Once the participants are enrolled, a third person, independent of the participant and investigator, will open the envelopes individually, and the executor will perform the corresponding injection per the envelope protocol.

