#### Clinical data collection and follow-up

2.4.3

Venous blood samples will be collected from participants at baseline and designated visit points for biochemical data, such as lipid, glucose, and uric acid. The method of venous blood sampling is as follows. First, the participants will fast for 10–12 h, and a qualified nurse will collect blood samples at 6:30–8:30 am. Next, the blood samples will be tested for 25(OH)D_2_, 25(OH)D_3_, and 25(OH)D levels using high-performance liquid chromatography-tandem mass spectrometry (LC-MS/MS) at the Fuzhou King Med Clinical Laboratory (Fuzhou, Fujian, China). The executive assistants involved in data collection and evaluation will be blinded to participants’ groupings. All clinical data collection processes are presented in **Table 2**.

**Table 2 T2:** Participant flow of enrolment, intervention, and outcome measurements.

		PS	M0	M1	M2	M3
Enrolment	Recruitment	√				
	Eligibility Screening	√				
	Signed written informed consent	√				
	Allocation		√			
Intervention	Health education, medical nutrition therapy, exercise therapy, self-monitoring of blood glucose, and disease follow-up		√	√	√	√
	High-dose vitamin D_2_ /placebo injection		√	√	√	
Outcomes	Demographic characteristics and basic information (sex, age, marital status, place of residence, and education level)		√			
	Personal life status (smoking status, drinking status, beverage intake status, sunshine reception, living alone, and menstrual status for females)		√			
	Duration of diabetes, strict diet control, and moderate aerobic exercise for >150 min per week		√			
	Number of self-monitoring of blood glucose per week and occurrence of hypoglycemia		√			
	Comorbidities (hypertension, hyperuricemia, obesity, osteoporosis, and nonalcoholic fatty liver disease)		√			
	Other diabetic complications (diabetic retinopathy, diabetic nephropathy, diabetic foot ulcer, coronary atherosclerotic heart disease, cerebrovascular disease, and peripheral vascular disease)		√			
	Anthropometric measurements (height, weight, body mass index, waist, and hip circumference) and blood pressure (systolic and diastolic blood pressure)		√			√
	Metabolic parameters (FBG, 2hBG, HbA1C, FCP, 2hCP, triglycerides, total cholesterol, HDL-C, LDL-C, uric acid, HOMA2-IR/%S/%B)		√			√
	Intima-media thickness of carotid and dorsalis pedis artery by ultrasound, fundus examination, bone mineral density		√			√

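### The data monitoring rule lets the study director see all results and decide when to end the trial, without keeping the director blinded or ruling out stopping on efficacy

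*Protocol article*

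**What the plan says.** Section 2.7 (Data monitoring) of the protocol article places the study under a hospital Ethics Committee, "whose members have no conflicts of interest with this study", and then states: "The study director will have access to all results and decide when to terminate the study based on its progress".

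Three other provisions bear on this:

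- **Blinding.** Section 2.2 says "we will double-blind the trial for the investigator and participants". Section 2.4.3 adds: "The executive assistants involved in data collection and evaluation will be blinded to participants’ groupings". Neither mentions the study director.
- **The director's other roles.** Under section 2.5, "all written materials and encrypted electronic files containing the study’s data will be stored and backed by the study director". Under section 2.4.4, "Serious adverse events will be reported to the study director" within 1 h.
- **Significance level.** Section 2.6 says "all statistical analyses will be performed using a two-sided test, considering P < 0.05 statistically significant".

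Table 2 schedules both the MNSI and the separate 25(OH)D2, 25(OH)D3 and total 25(OH)D assays at baseline (M0) and 3 months (M3). Section 2.3 gives vitamin D2 to the active arm and sodium chloride to the placebo arm.

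**The concern.** One sentence gives one person both sight of the results and the decision to end the trial. The only stated criterion is the study's progress, which does not separate recruitment and safety from efficacy. Because the sentence is a positive rule, the point is what it permits. It is not that a condensed article lacks a look schedule or a stopping boundary.

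Two things are at stake. If the trial were stopped because the MNSI comparison looked favourable, the final test at 0.05 would no longer have a 5% error rate and the estimated effect would tend to be too large. Separately, someone who knows the emerging results by arm can influence recruitment, retention and the handling of events, even without meaning to. No later analysis can restore the blind, and a reader of a trial that ended early could not tell a planned end from a chosen one.

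**Working it through.** **1. The plan's own figures.** Inputs from section 2.1.3: difference 1.19, SD 1.29, two-sided alpha 0.01, power 0.95, two equal groups.

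n per group = 2 × (z₀.₉₉₅ + z₀.₉₅)² × (SD/difference)² = 2 × (2.576 + 1.645)² × (1.29/1.19)² ≈ 41.9, so 42 per group and 84 in total.

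With 20% loss: 42/0.80 = 52.5, so 53 per group and 106 in total.

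Both match the article, so no stated figure is wrong on this point.

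**2. Is the director blinded?** Section 2.2 blinds the investigator and the participants, and section 2.4.3 blinds the assistants who collect and evaluate data. There are two readings:

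- If the director counts as an investigator, access to all results has to be squared with the blind.
- If not, nothing in the article blinds the director.

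Either way, a sentence is needed.

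**3. Could the results show the arm without the randomisation code?** Very likely.

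- The active product is vitamin D2 and the placebo is saline (section 2.3).
- 25(OH)D2 is reported separately by LC-MS/MS (section 2.4.3).
- Recent vitamin D use is an exclusion criterion (Table 1), and participants are told to avoid mushrooms and similar foods (section 2.8).
- The Discussion notes that measuring D2 removes the influence of sunlight.

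A raised M3 25(OH)D2 would therefore point to the active arm. The MNSI is scored at the same visit, so anyone holding both results could form the between-arm comparison.

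**4. Could results accumulate before the trial ends?** The endpoint is at 3 months, and the Discussion expects recruitment to be difficult. Early participants could reach M3 while others are still being enrolled.

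**5. Size, if efficacy looks occurred.** The documents give no number of looks, so it is varied. Each scenario used 200,000 simulated trials with no true difference. A two-sample t-test at two-sided 0.05 was applied at each look, and the trial stopped at the first significant result. Looks were equally spaced, rounded to whole participants per group. The Monte Carlo standard error is at most 0.1 percentage points.

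| Looks in total, including the final one | 42 per group | 53 per group |
|---|---|---|
| 1 | 5.0% | 5.0% |
| 2 | 8.4% | 8.3% |
| 3 | 10.9% | 10.8% |
| 4 | 12.8% | 12.9% |
| 5 | 14.6% | 14.3% |
| After every pair, from 10 per group | 20.3% | 22.7% |

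The 0.05 level comes from section 2.6, whereas the sample size used 0.01. At 0.01 the pattern is the same: 1.0% becomes about 1.8% with 2 looks and 3.3 to 3.4% with 5.

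**6. Size, if no efficacy looks occurred.** If no between-arm efficacy result is examined before the end, or if stopping depends only on safety, futility or recruitment, the error does not rise above 5%.

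**The case against.** The sentence can be read innocently. Progress may mean recruitment, conduct or safety. The next sentence in section 2.7 concerns publication, so access to results may mean access to the final data. The Ethics Committee supervises the trial. Someone independent of the research center generates the code, and a third person opens the envelopes. Storing files and receiving serious adverse event reports are ordinary duties. The post-baseline 25(OH)D2 assay comes after the last injection, so it cannot alter that participant's treatment, and nothing says that assay results reach the director before database lock. The article plans no interim analysis.

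Much of this stands, and it rules out several stronger readings that a reader might infer:

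- **That the director may stop at will.** The text ties the decision to the study's progress.
- **That the director is unblinded, or that the double-blind statement is contradicted.** No section gives the director the code. The two statements are left unreconciled, which is a weaker fault.
- **That the false-positive rate is in fact inflated.** That would require between-arm results to be seen and a favourable one to trigger stopping. No section plans either.

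The objection does not remove the point itself. The sentence sits under data monitoring and governs when the study ends, so confining it to the final dataset is a strained reading. Supervision by the Ethics Committee does not move the decision away from the director. Independent custody of the code gives limited protection if separate D2 values are among the results the director may see.

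**Conclusion.** The point holds as a fault in what the rule permits. Section 2.7 joins access to all results with the termination decision, does not confine that access to blinded or pooled data, and does not exclude efficacy as a reason to stop. The blinding statements do not cover the director by name.

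If the permission were used for unadjusted looks at the MNSI comparison, the nominal 5% error would become about 8% with 2 looks in total, 11% with 3 and 14 to 15% with 5. These figures assume equally spaced looks and stopping at the first P < 0.05. If it were not used that way, the error stays at 5%.

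This should be fixed, but it does not show that the trial is invalid. Confidence is moderate, because the article leaves open what the director will actually see, and when.

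**What to change.** Reword section 2.7 to state that:

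1. no interim between-arm efficacy analysis will be done;
2. the trial ends when the planned 106 participants have been enrolled and followed to M3;
3. the director and the investigators will not see arm-level outcomes or post-baseline 25(OH)D2 and 25(OH)D3 results until database lock;
4. any earlier termination will not rest on between-arm efficacy results and will be made under the supervision of the existing Ethics Committee.

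Termination need not be limited to safety, since stopping for recruitment or futility does not raise the error above 5%. No new role is needed for the person who generates the randomisation code.

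The cost is protocol wording and an arrangement with the laboratory to hold back the post-baseline D2/D3 results. The director loses some discretion and early sight of those results. The sample size and visit schedule do not change.
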